### Outcomes

The primary endpoint is the percentage change in the FM-UE defined as 90 days FM-UE minus initial FM-UE, divided by initial FM-UE impairment:$$\frac{\mathrm{FMUE}\left(90\ \mathrm{days}\right)-\mathrm{FMUE}\left(\mathrm{initial}\right)}{66-\mathrm{FMUE}\left(\mathrm{initial}\right)}\times 100\%$$

The FM-UE [25] is a highly standardized, reliable and validated clinical score to assess deficits in upper extremity function after stroke [26]. The primary endpoint will allow to measure to what extent a given participant will deviate from the predicted proportional recovery rule of 70% improvement of the initial FM-UE impairment [19].

Secondary endpoints are the changes in the following tests 90 days after the stroke event compared to the initial test results within 96 h after stroke onset:Action research arm test (ARAT) [21]: to measure recovery of function of the UEModified Rankin scale (mRS) [22]: to measure neurological impairmentBarthel index (BI) [23]: to measure performance in activities of daily livingSS-QOL scale [24]: to measure quality of life and demonstrate the influence of the scores described above on the personal experience of the patient

All of these tests have shown reliability and have been validated in the assessment of patients post-stroke [22, 24, 27, 28].

### Participant timeline

In the first 96 h after stroke onset the primary data set (see below) is acquired by the University Hospital of Tübingen, or one of the other cooperating acute-care hospitals.

0–24 h: The patients will be screened for participation, written informed consent will be obtained, the first clinical tests will be conducted adapted to the patient’s fitness, and a blood sample (part of the usual stroke workup) is collected.

25–48 h: Neuroimaging (magnetic resonance imaging (MRI) or computed tomography (CT)) will be conducted and further clinical tests adapted to the patient’s fitness will be performed.

49–96 h: Adapted to the patient’s fitness, clinical tests, EEG and motor evoked potentials (MEPs) will be performed.

After completion of acute stroke treatment, participants are transferred to collaborating neurorehabilitation facilities. There, the rehabilitation data set is collected:

On admission: FM-UE, BI and mRS.

During the stay:At intervals of 14 days: FM-UE, BI and mRSnumber, duration and type of neurorehabilitative treatments

On discharge:FM-UE, BI and mRS

Final examination:

After 90 days the final follow-up examination is carried out. The following data is collected: FM-UE (primary endpoint), ARAT, BI, mRS, SS-QOL scale (secondary endpoints).

There are no interventions planned in this observational study. All participants are treated according to the current guidelines, the same way they would have been treated outside of this study.

### Sample size

We will use machine learning algorithms to predict the primary end point (i.e., the change in FM-UE 90 days after the stroke event compared to the initial FM-UE, see definition under “Outcomes”) as a function of the primary data set and the rehabilitation data set detailed in Tables 2, 3. Model development will start once 50 patients have been reached and continue throughout the study. To cope with the dimensionality of the problem, we will use lasso-regularized linear regression to select a sparse subset of the potentially correlated features. We will use a nested-cross validation setup to tune the regularization strength via the 1SE-rule [29] and obtain estimates of the fraction of the explained variance of the total variance in the primary end point on data not seen during model training. Due to the exploratory nature of the project and the complex models involved, a precise sample size calculation is not feasible.

**Table 2 Tab2:** Timeline for collecting the primary data set in the university hospital and other study sites

		Clinical data	Imaging data	Electrophysiological data	Laboratory data
0–24 h		NIHSS*			Blood sample*
25–48 h		mRS*	MRI* or CT*		
49–96 h		SAFE score		EEG	
				MEP	
		Grip strength			
		FMA			
		ARAT			
		BI*			
		Bells test			
		AST			
		BDI			
		SS-QOL scale			

Tests marked with * are part of the usual stroke work-up

Abbreviations: *NIHSS* National Institute of Health Stroke Scale, *mRS* modified Rankin Scale, *SAFE* Shoulder Abduction Finger Extension score, *FMA* Fugl-Meyer Assessment, *ARAT* Action Research Arm Test, *BI* Barthel Index, *MRI* magnetic resonance imaging, *CT* computed tomography, *Aphasie-Schnelltest, AST* aphasia quick test, *BDI* Beck’s Depression Inventory, *SS-QOL* Stroke-Specific Quality Of Life scale, *EEG* electroencephalography, *MEP* motor evoked potential

**Table 3 Tab3:** Overview over complete data collection

Location	Time point	Data set
University hospital of Tübingen, other recruiting study sites	Day 1–4 after stroke	Primary data set (see Table 1)
Rehabilitation hospital	On admission	Rehabilitation data set: FM-UE, BI and mRS
	Every 14 days during the stay and on discharge	• FM-UE, BI, mRS and questionnaire to capture soft influencing factors • Number, duration and type of neurorehabilitative treatments
University hospital	Day 90 after stroke	FM-UE, ARAT, BI, mRS, SS-QOL scale

Abbreviations: *FM-UE* Fugl-Meyer upper extremity score, *BI* Barthel Index, *mRS* modified Rankin Scale, *ARAT* Action Research Arm Test, *SS-QOL* Stroke-Specific Quality Of Life scale

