## Methods

### Objectives

The objective of the present study is to identify factors predicting motor outcome after stroke more accurately than hitherto possible, and rehabilitation treatments that are associated with improvement of arm−/hand function in individual motor stroke patients, using machine learning algorithms.

Primary objective: To determine which factors of the primary data set within 96 h of stroke onset and which type and amount of rehabilitation treatment predict the primary endpoint, i.e., the change in the FM-UE defined as 90 days FM-UE minus initial FM-UE, divided by initial FM-UE impairment.

Secondary objectives: Secondary endpoints are the quality of life, independence and range of activity of the UE measured by stroke-specific quality of life (SS-QOL) scale, modified Rankin Scale (mRS), Barthel-Index (BI) and Action Research Arm Test (ARAT) 90 days after the stroke event compared to the initial scores in the acute phase.

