### Statistical methods

Statistical methods for primary and secondary outcomes.

Only those participants will a complete data set (including the 90 days follow-up examination or a lethal outcome) will be included in the statistical data analysis. Previous studies suggested that the FM-UE endpoints (i.e., the change in FM-UE 90 days after the stroke event compared to the initial FM-UE, see definition under “Outcome”) or the recovery trajectories of FM-UE scores can be clustered into 3 to 5 subgroups [4, 40]. We will first use time series clustering methods such as mixture of Gaussian processes [41] to identify such subgroups, then use the inferred cluster labels to build a classifier using lasso-regularized logistic regression to predict the group membership of the patient as a function of the primary data set and rehabilitation data set detailed in Tables 2, 3. The lasso regularization can automatically select a sparse subset of the significant features, reducing the dimensionality of the feature space and potentially the sample size required. We will use a nested-cross validation setup to tune the regularization strength via the 1SE-rule [29]. We can then use the Gaussian process model of the respective group to predict the primary endpoint and obtain estimates of the fraction of the explained variance of the total variance in the primary end point on data not seen during model training. If the linear model proves insufficient or unsatisfying, we will resort to non-linear regression models such as Generalized Additive Models (GAMs), which allow flexible nonlinear transformations of individual features of pairs of features [42]. Models for secondary endpoints will be built as well.

Interim analyses are not planned since this an observational study without interventions. No further analyses are planned apart from what is described under statistical methods for primary and secondary endpoints. Biobanking of blood samples will allow future (not yet planned) analyses of the relation of blood markers to stroke rehabilitation outcome.

Methods in analysis to handle protocol non-adherence and any statistical methods to handle missing data.

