## Discussion

The primary objective of the present study is to identify markers in the acute phase of stroke predicting recovery of UE motor function and determine the most suitable neurorehabilitative treatment in a given patient based on the acquired data sets using machine learning algorithms.

Although we aim to include the whole spectrum of stroke patients (with a FM-UE ≤ 50 points, indicating a relevant deficit), it is possible that the majority of recruited patients will have relatively mild impairment as the whole test battery and the additional electrophysiological examinations might be viewed as strenuous, particularly for severely affected patients. Thus, the data set might be biased towards less affected patients. However, some of the clinical tests and the neuroimaging are part of the usual stroke work-up anyways, and the additional clinical and electrophysiological tests are designed to be executed with a minimal amount of active participation. Thus, we assume that we will be able to collect sufficient data of severely affected stroke patients, in order to draw generalizable conclusions from the study findings.

Whereas the collection of the primary data set in the stroke units is relatively straightforward, it might be more difficult to encompass the rehabilitation process, which is heavily influenced by motivation of the patient and support by relatives. Therefore, we invested a lot of effort in creating items for documenting these aspects of the rehabilitation process by a questionnaire capturing these potentially influencing factors. Hence, we assume we will be able to gather a comprehensive data set of the rehabilitation process.

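### One lasso penalises acute severity and therapy features together, so where therapy varies with severity it can select therapies that have no effect; such selection supports prediction, not a reading as significance or treatment choice

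*Protocol article*

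**What the plan says.** Under Objectives, the primary objective has two halves: which acute factors predict the primary endpoint, and "which type and amount of rehabilitation treatment predict the primary endpoint".

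Under Sample size, the endpoint is modelled "as a function of the primary data set and the rehabilitation data set detailed in Tables 2, 3". The estimator is a lasso ("we will use lasso-regularized linear regression to select a sparse subset of the potentially correlated features"), and its penalty is set as follows: "We will use a nested-cross validation setup to tune the regularization strength via the 1SE-rule". No feature is named as forced in or left unpenalised.

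Statistical methods describes a second route, in which patients are first clustered and a logistic lasso then has this task: "predict the group membership of the patient as a function of the primary data set and rehabilitation data set detailed in Tables 2, 3". Its joint feature set is the same. That section says of the result: "The lasso regularization can automatically select a sparse subset of the significant features". It also rules out analyses beyond those it describes.

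The Discussion restates the primary objective as including to "determine the most suitable neurorehabilitative treatment in a given patient based on the acquired data sets using machine learning algorithms".

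Participant timeline says that care is guideline-based and unaffected by the study, so therapy is not randomised. The Background says that outcome depends on clinical severity. It also says that rehabilitation procedures are usually fixed and depend little on stroke type, location or severity. No correlation between therapy and severity is given anywhere.

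**The concern.** Prediction and the assessment of a therapy ask different things of a model. For prediction, a therapy that stands in for severity is harmless and may help. To say that a therapy relates to recovery beyond the patient's initial state, the severity adjustment has to be complete, and a lasso shrinks it on purpose. The 1SE rule shrinks more than the cross-validation minimum does. Any therapy correlated with severity can then take up what the penalty left unexplained. This differs from ordinary chance selection because it grows with the strength of confounding.

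At stake is the list of therapies produced for the rehabilitation half of the primary objective. The plan calls selected features significant and hopes to guide treatment choice with them.

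**Working it through.** **Plan's own figure.** There is none to reproduce: no error rate, effect size or explained variance is stated for the lasso.

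**Inputs from the protocol.** Joint feature set, lasso and 1SE rule; 200 patients (Abstract and Table 1); model development from 50 patients (Sample size).

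**Assumptions, because the documents are silent.** Therapy–severity correlation ρ from 0 to 0.7; share of endpoint variance explained by severity (R²) 0.3 to 0.5; six acute severity scores with pairwise correlation r of 0.7 or 0.5; four therapies correlated ρ with severity; four unrelated therapies; 30 noise features. All therapies have zero effect.

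**Why it can happen.** Let the endpoint be bD + error, where D is the standardised mean of k severity scores. Each score correlates with D by c = √(r + (1−r)/k). In a very large sample the lasso fits aD, with (b−a)c = λ. A zero-effect therapy then has covariance (b−a)ρ = λρ/c with the residual, and it enters once this exceeds λ, that is once ρ > c. Below that, sampling error decides, and entry becomes likelier as ρ/c nears 1.

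- Six scores, r = 0.7: c = √(0.7 + 0.3/6) = 0.866; at ρ = 0.7, ρ/c = 0.81.
- Six scores, r = 0.5: c = √(0.5 + 0.5/6) = 0.764; at ρ = 0.7, ρ/c = 0.92.
- One score carries everything: c = 1; at ρ = 0.7, ρ/c = 0.70.

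**Simulation.** 10-fold cross-validation, 1SE rule, n = 200. The chance that at least one of the four ineffective severity-linked therapies is selected:

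| Structure | ρ = 0 | 0.3 | 0.5 | 0.7 |
|---|---|---|---|---|
| One measured score drives outcome, R² 0.3–0.5 | 1% | 1–2% | 4% | 10–17% |
| Mean of six scores, r 0.7, R² 0.3–0.5 | 1–3% | 2–4% | 11% | 41–45% |
| Mean of six scores, r 0.5, R² 0.5 | not run | 9% | 32% | 84% |
| Six measured scores, R² 0.4 (separate simulation) | 3% | 10% | 25% | 52% |
| Latent severity, scores measured with error, R² 0.3–0.5 | 1–2% | 6–7% | 17–27% | 51–81% |

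All rows except the separate simulation used 200 data sets per setting, so the Monte Carlo standard error at 11% is √(0.11 × 0.89/200) = 2.2 points. The ordering at ρ = 0.7 for the measured-score rows (10–17%, 41–45%, 84%) follows ρ/c (0.70, 0.81, 0.92). Therapies unrelated to severity were each selected at most 1% of the time at n = 200.

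**Same data, severity scores unpenalised.** 0–2% at n = 200 in every setting. In the separate simulation it was 0%, against 3%, 10%, 25% and 52% for the joint lasso.

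**At n = 50** (six scores, r = 0.7, R² 0.5): 6%, 23% and 46% at ρ = 0, 0.5 and 0.7, against 1–4% with severity unpenalised.

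**Sensitivity to structure, upwards.** Designs with 40 acute features, two of them with the features uncorrelated, gave 18–97% at ρ = 0.3 and 59–100% at 0.5. The formula explains this: with 8 uncorrelated prognostic features, c = √(1/8) = 0.354, so ρ/c is 0.85 at ρ = 0.3 and above 1 at 0.5. Several of the plan's clinical scores measure overlapping arm impairment, so I do not take these rates as the size of the problem.

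**Sensitivity to structure, downwards.** Adding a rehabilitation-stage FM-UE score that tracks prognosis and outcome brought the joint lasso to 3% at ρ = 0.3. In another design an assumed strongly informative score of this kind gave 2% at 0.3 and 3% at 0.5.

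**Sign.** With ρ positive, the selected coefficients favoured therapy. With ρ reversed, every selected ineffective therapy looked harmful.

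**The case against.** The strongest reply is that the key premise is not in the documents. No section says that therapy is chosen by severity, and the only remark on the point, in the Background, says largely the opposite. That stands as a limit on size. It does not remove the mechanism. The remark concerns procedures in general, whereas the features include number and duration of treatments. Assessments continue until discharge, and some patients are still in rehabilitation at day 90, so amount can vary with the patient's state.

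Second, the stated aim is prediction: Objectives speaks of predicting and of association, Trial design calls the framework exploratory, and success is measured by held-out explained variance. That stands for the joint lasso as a predictor. It does not cover reading selected features as significant or choosing treatment from them.

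Third, the rehabilitation data set contains repeated FM-UE, BI and mRS scores, which absorb much of the leftover severity signal. This stands and lowers the rates. It is not a substitute for proper adjustment, because scores taken during rehabilitation may themselves be affected by therapy.

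Fourth, the endpoint is already divided by initial impairment, so the assumed R² may be too high. That is fair, and R² is an assumption. With six scores at r 0.7, R² of 0.3 and 0.5 gave nearly the same rates.

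Fifth, penalty details often belong in an analysis plan. But the article states the method itself and excludes further analyses, so this is more than omitted detail.

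A reader might also set 59% selection by the joint lasso (ρ = 0.5, 40 acute features) beside about 5% rejection under double selection. The first figure is for any of four therapies, the second for one. Assuming rough independence, double selection gives 1 − (1 − 0.047)⁴ = 17.5% at ρ = 0.5. At ρ = 0.3 it gives 1 − (1 − 0.053)⁴ = 20%, against 18% for the joint lasso. Double selection therefore needs a multiplicity statement.

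**Conclusion.** The concern holds in a conditional form. One lasso serves both halves of the primary objective with no protected severity adjustment. If therapy varies with the patient's state, ineffective therapies can be selected even when all confounders are measured. At 200 patients with the 1SE rule, the chance of selecting at least one of four is about 1–10% at correlation 0.3 or below, about 4–32% at 0.5 and about 10–84% at 0.7. It is lower with rehabilitation-stage FM-UE scores in the model. The ranges rest on assumed correlations, R² and feature structure, include settings where severity is measured with error, and were obtained for the linear model. The clustered logistic version shares the feature set and the reasoning but was not simulated.

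Two stronger readings are tempting, and the documents support neither. One is that ineffective therapies will be listed: no therapy–severity correlation is given, and the Background points to a weak one. The other is that the error always favours therapy: the sign depends on whether fitter or more impaired patients receive more of it, which the documents do not say.

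A change is worth making, because the rehabilitation half of the objective has no other analysis and the remedy is cheap.

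**What to change.** - Keep the joint lasso for prediction only, and say so. Drop the description of selected features as significant, and do not use selection to determine the most suitable treatment.
- For the rehabilitation half of the objective, add a therapy analysis that leaves the acute severity features unpenalised. Alternatively use double selection: one lasso of the endpoint on the acute features, one of each therapy variable on the acute features, then an unpenalised regression of the endpoint on the therapy and the union of the selected acute features.
- Report confidence intervals, with a statement on multiplicity across therapies.
- Report the gain in held-out explained variance of acute-plus-therapy over acute-only.

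The cost is a few sentences and some extra fits on data already being collected. The downsides are wider intervals and probably fewer therapies named. Confounding by unmeasured factors remains, and the text should say so.

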### Recruitment

All acute stroke patients (> 2000 per year in the University Hospital of Tübingen and the 4 cooperating acute-care hospitals of the Center of Neurovascular Diseases) will be screened for recruitment, which is planned for a duration of 1.5 years. Up to 70% of all stroke patients present with UE paresis [2, 30], thus about 2000 patients (2000 patients /year × 1.5 years (recruitment period) × 0,7 (percentage of patients presenting with affection of UE)) are available for recruitment in theory. In practice (according to a preparatory analysis of our stroke unit data base over the preceding 2 years), approximately 60% of these patients will not have a sufficient deficit defined as FM-UE ≤ 50 initially or they will have a sufficient deficit, but it will not lasting beyond 96 h resulting in the patient not being in need of rehabilitation of the UE and not eligible for the project anymore (since he or she is not meeting the inclusion criteria anymore), or will die or be too frail for rehabilitation treatment, or will not fulfil the inclusion/exclusion criteria to begin with. Out of the remaining group of 800 patients there will be an expected further attrition by approximately 50% due to unwillingness to participate in the study or failure to obtain written informed consent, leaving approximately 400 patients for recruitment (i.e., a safety margin of 100 patients given the planned inclusion of 300 patients).

Unfortunately, the recruitment process showed that despite the conservative calculation we will probably only reach 200 patients.

### Data collection and management

#### Plans for assessment and collection of outcomes

Each participant will be assessed carefully within the first 96 h after stroke onset in the acute-care hospitals, using an extensive battery of standardized and validated clinical tests and scores. Additionally, laboratory, neuroimaging and electrophysiological data will be obtained. These data constitute the primary data set. In the rehabilitation hospitals some of the clinical scores of the primary data set will be obtained repeatedly at 14 days intervals, and the amount, type and intensity of neurorehabilitation treatment will be documented. These data constitute the neurorehabilitation data set. All data will be managed and integrated in a customized secure clinical data capture system (REDCap®, Research Electronic Data Capture) to which some of the data will be transferred automatically from primary clinical data information systems, while other data will be inserted manually.

All of the following clinical tests are conducted by or under the supervision of a qualified medical doctor of the University Hospital of Tübingen (Department of Neurology), a collaborating acute-care hospital of the Centre of Neurovascular Diseases, or a cooperating rehabilitation facility. Diagnostic neuroimaging is performed by a qualified medical doctor of the department of neuroradiology of the University Hospital of Tübingen or a trained medical doctor of the collaborating hospitals. All electrophysiological tests are performed by or under the supervision of a qualified medical doctor of the University Hospital of Tübingen, department of neurology, or of the collaborating hospitals.

